### Inclusion criteria

Term and near term infants (36–43 weeks gestation) with evidence of neonatal encephalopathy and treated with therapeutic hypothermia at the participating neonatal units will be eligible for recruitment.

### Exclusion criteria

Life-threatening congenital malformationsSyndromic infants, and babies with neurometabolic diseasesNeurodevelopmental follow-up not possibleDeath/withdrawal of life support before completion of 72 h of therapeutic hypothermiaLack of parental consent or inability to scan within 2 weeks of birth

### Clinical assessment

All infants will have standard intensive care management for neonatal encephalopathy. Gestational age; birth weight and head circumference; the Apgar score at 1, 5 and 10 min; umbilical cord pH; base deficit and Lac or blood gas pH; base deficit; Lac within 1 h of birth will be recorded. The babies will have a cranial ultrasound scan on admission, at 24 h and 3–4 days for detection of malformations, bleeds, loss of normal tissue differentiation and evolving tissue injury.^26^ Amplitude-integrated EEG (aEEG) will be performed over the first 48 h, as part of standard clinical care. The aEEG background activity will be classified according to voltage criteria and by background pattern.^27^ We will perform a scored neurological assessment (National Institute of Child Health and Human Development scoring system^28^
^29^), on admission, daily during the first 3 days and an additional more detailed assessment before discharge. Additional items will include: head circumference, head control, axial tone, limb tone, seizures, visual fixation and following, squint, hearing, feeding.

### MRI protocol

#### Acquisition

MRI will be performed between 4 and 14 days after birth (ie, after completion of therapeutic hypothermia) in all infants, following informed parental consent. Existing MR scanning protocols will be followed in the individual centres with regard to sedation and monitoring.

#### MRI

Detailed MR sequences for different scanners will be developed into individual MR taskcards at each site. Typical MR parameters on a Philips 3 T scanner are: T1-weighted three-dimensional (3D) magnetisation-prepared rapid gradient-echo (sagittal, repetition time (TR)=17 ms, echo time (TE)=4.6 ms, flip angle=13°, inversion time=1465 ms, 0.8×0.8×0.5 mm^3^ voxels), T2-weighted 2D turbo spin echo (axial, TE=130 ms, TR=8800 ms, 0.5×0.5×3 mm^3^ voxels) and diffusion tensor imaging (DTI; 32 direction 2D spin-echo echo-planar imaging, b=750 s/mm^2^, TR=7860 ms, TE=49 ms, 1.75×1.75×2 mm^3^ voxels, SENSE factor ×2).

#### Conventional MRI score

Each image will be reported systematically by an experienced neonatal neurologist blinded to the clinical history but not gestational age and age at scan. Each scan will be assessed for anatomy, established injury, atrophy, haemorrhage and ventriculomegaly. Based on the scoring system developed by Rutherford *et al*,^30^ brain tissue injury will be scored from 0 to 3 for basal ganglia/thalami, white matter and cortex (0=normal, 1=mild signal abnormality, 2=moderate signal abnormality, 3=severe signal abnormality) and the posterior limb of the internal capsule scored from 0 to 2, as normal, equivocal or abnormal. The presence of focal hemispheric lesions and their site will also be noted.

#### MRS metabolite peak area ratios

Single-voxel point-resolved spectroscopy (PRESS), 15×15×15 mm^3^ cubic voxel in the left thalamus, TR=2288 ms/TE=288 ms (16 averages with 8 phase cycles, water suppressed) and TR=2060 ms/TE=60 ms (8 averages with 8 phase cycles, water suppressed). Metabolite peak area ratios involving NAA, total choline, total creatine and Lac will be derived.

#### MRS quantification of [NAA]

Same thalamic voxel; additional PRESS scans: (1) TE=60 ms, TR=5000 ms, (8 averages with 8 phase cycles, water suppressed) (2) TE=60, 124, 205, 316, 495, and 1000 ms, each with TR=10s+TE, with one average of eight phase cycles, and without water suppression. NAA concentration will be derived from an assumed brain water concentration by comparing the T2-corrected fully relaxed NAA and brain water signals.

#### TBSS analysis

Whole-brain white matter FA with TBSS will be analysed using the Functional MRI of the Brain Software Library (FSL, V.4.1)^31^ and the Diffusion Tensor Imaging ToolKit (DTI-TK, V.2.3.1).^32^ Diffusion-weighted data will be corrected for motion and eddy current distortion, segmented to exclude extracerebral tissue, and used to reconstruct the diffusion tensor volume, with FSL. The diffusion tensor volumes from all the participants will be spatially normalised with an optimised pipeline in DTI-TK, prior to TBSS analysis.^33^ An FA threshold (>0.10) will be required to identify the major white matter tracts but to exclude peripheral tracts. TBSS will be used to assess the relationship between FA and outcome. The presence of group-wise FA differences with p<0.05, corrected for multiple comparisons using threshold-free cluster enhancement,^34^ will be considered statistically significant.

#### MR Spectroscopy Analysis

The raw data will be taken from MR scanners, postprocessed using software developed in-house, and LCModel (LCModel Inc, Oakville, Ontario, Canada, V.6.1) will be used to calculate metabolite peak area ratios and concentrations.

### Neurodevelopmental outcome

A standardised, validated and scorable neurological examination will be performed;^35^ the presence and type of cerebral palsy determined according to Gorter *et al*^36^ and severity classified using the Gross Motor Function Classification System (GMFCS). Neurodevelopmental outcome will be assessed using the Bayley Scales of Infant Development (BSID-III), by trained and certified examiners. Vision and audiometric evaluations^37^ will be collected alongside anthropometric data (weight, height and head circumference) as part of the follow-up evaluations. Infants will be tracked and undergo follow-up at network centres with evaluations at 18–24 months.

Outcome will be assessed according to the neurological examination score; the GMFCS level; and the cognitive, language and motor composite scores. These variables provide quantitative data that can be compared with MR measures.

Severe disability will be defined as any one of the following: Bayley III, both cognitive and language composite scores <70, GMFCS level 3–5, hearing impairment requiring hearing aids or blindness. Moderate disability will be defined as both cognitive and language composite scores between 70 and 84 and one or more of the following: GMFCS level 2, hearing impairment with no amplification or a persistent seizure disorder.

The outcomes will also be assessed by categorisation of these scores and by including mortality as an outcome. Adverse outcome will be defined as death or, in survivors, moderate or severe disability.

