### Sample size calculation and data analysis

The primary outcome will be unfavourable outcome at 18–24 months (yes/no). Approximately 50% of the infants are expected to have an unfavourable outcome. Since this is binary, multivariable logistic regression will be used to develop risk prediction models. The predictors in these models will be: [NAA], Lac/NAA peak area ratio, white matter FA (all continuous); aEEG at 48h (categorical with three levels) and clinical examination at discharge (binary). Models will be validated using 10-fold cross-validation, and will be assessed with respect to calibration and discrimination. Calibration and discrimination will be measured using calibration slopes and receiver operating characteristic curves, respectively. Shrinkage techniques will be used to adjust for overfitting, thus improving calibration. Sensitivity and specificity will be calculated at selected cut-off points.

The sample size is calculated using the ‘rule of 10’,^2^ generally used to calculate the sample size requirements for developing prognostic models. The multivariable risk model will contain seven predictors that are modelled using nine parameters to examine the incremental benefits of various clinical, bedside (aEEG) and MR biomarkers (conventional MR reporting, MRS peak area metabolite ratios and [NAA]). Considering nine parameters, we require 9×10 adverse events, which suggest that a total sample size of 180 is required.

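### The disability definition is not monotone: lowering one Bayley composite below 70 can move a child from adverse to not adverse

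*Protocol article*

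**What the plan says.** The definitions are in the protocol article, section Neurodevelopmental outcome.

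- **Severe:** any one of "Bayley III, both cognitive and language composite scores <70, GMFCS level 3–5, hearing impairment requiring hearing aids or blindness".
- **Moderate:** "Moderate disability will be defined as both cognitive and language composite scores between 70 and 84 and one or more of the following". The list of further features, at least one of which the child must have, then reads "GMFCS level 2, hearing impairment with no amplification or a persistent seizure disorder".
- **Binary endpoint:** "Adverse outcome will be defined as death or, in survivors, moderate or severe disability".

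The section Sample size calculation and data analysis then uses this variable: "The primary outcome will be unfavourable outcome at 18–24 months (yes/no"). It also states the expected rate: "Approximately 50% of the infants are expected to have an unfavourable outcome".

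**The concern.** Each Bayley criterion requires the two composites to lie in the same band: both below 70 for severe, both at 70–84 for moderate. No rule is given for composites in different bands. For one such pattern, one score below 70 and the other at 70–84, the effect is more than a gap in coverage. It reverses the order of severity. A child who already counts as adverse through the moderate rule stops counting if one composite falls below 70 while the other stays at 70–84. No severity scale can intend that.

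The variable is the reference standard for the logistic models, calibration slopes, ROC curves, sensitivity and specificity. Children misplaced into the favourable group enter all of these. The sample size also counts events on the same variable.

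**Working it through.** **1. The plan's own figure.** Inputs from Sample size calculation and data analysis: nine parameters, 10 events per parameter, 50% unfavourable.

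N = 9 × 10 / 0.50 = 180, as stated, and 180 × 0.50 = 90 events. The figure reproduces and is not in error on this point. It leaves no margin above 90 events.

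**2. The rules applied literally.** Let C and L be the cognitive and language composites.

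- Severe = (C < 70 and L < 70) or GMFCS 3–5 or hearing aids or blindness.
- Moderate = (70 ≤ C ≤ 84 and 70 ≤ L ≤ 84) and (GMFCS 2 or unaided hearing impairment or persistent seizures).
- Adverse = death or severe or moderate.

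The survivors below have no GMFCS 3–5, hearing aids or blindness:

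| C / L | Listed moderate item | Severe? | Moderate? | Class |
|---|---|---|---|---|
| 75 / 75 | GMFCS 2 | no | yes | adverse |
| 65 / 75 | GMFCS 2 | no, L is not < 70 | no, C is not 70–84 | **not adverse** |
| 65 / 65 | GMFCS 2 | yes | – | adverse |
| 75 / 75 | none | no | no | not adverse |
| 65 / 75 | none | no | no | not adverse |

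The first three rows show the reversal: adverse, then not adverse, then adverse again as scores fall. The last two show that without a listed item there is no reversal, since neither child is adverse.

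**3. Exhaustive check.** All combinations of three score bands for each composite, GMFCS (0, 1, 2, 3–5), hearing (normal, unaided impairment, aids), blindness and seizures were classified: 3 × 3 × 4 × 3 × 2 × 2 = 432 profiles. The search was for pairs in which one child is at least as impaired on every item, yet is not adverse while the other is.

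- Current wording: 68 reversed pairs. In all of them the worse child has one score < 70 and the other at 70–84, and the better child has both at 70–84.
- With GMFCS 0 and 1 merged (324 profiles): 38 reversed pairs. The count depends on the coding; the existence of the reversal does not.
- With the moderate score condition changed to both composites < 85: 0 reversed pairs under either coding.

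**4. Upper bound on the children affected.** The document gives no score distribution, so these inputs are assumptions: C and L bivariate normal with a common mean of 85, 90 or 95, SD of 15 or 18, and correlation 0.6, 0.75 or 0.85 (18 settings); 160 survivors (180 less an assumed 20 deaths).

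Share in the mixed band = 2 × [P(C < 70, L < 84) − P(C < 70, L < 70)].

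- Lowest: 3.9% (mean 95, SD 15, r 0.85); 0.039 × 160 ≈ 6 children.
- Highest: 13.1% (mean 85, SD 18, r 0.6); 0.131 × 160 ≈ 21 children.
- Middle setting (mean 90, SD 15, r 0.75): 7.4%, about 12 children.
- With the upper cut at 85 instead of 84, the range is 4.0–13.8%.

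This band includes children with no listed item (not reversed) and children already severe through GMFCS 3–5, hearing aids or blindness (correctly adverse). If 10–30% of the band had a listed item and no severe criterion, a further assumption, the number reversed would be 0.10 × 6 = 0.6 to 0.30 × 21 = 6.3 children. If 1 to 6 children were lost from 90 events, 89/9 = 9.9 to 84/9 = 9.3 events per parameter would remain.

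**The case against.** **The size is not established.** The means, SDs, correlations, normality and survivor count are all supplied by this review, and the reversal needs a listed item that many children in the mixed band may not have. This stands. The 4–13% is only an upper bound, and the true number cannot be derived from the document.

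**The composites are also analysed as quantitative data.** The Neurodevelopmental outcome section plans to compare GMFCS level, neurological score and composite scores with the MR measures. Those analyses do not depend on the categories. This is true, but the prediction models use the yes/no outcome.

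**The article is condensed.** The full protocol may say either, or have a residual category. That cannot be checked here. The printed rule is explicit and complete enough to apply, and applied as printed it misorders children.

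**Stronger readings that the document does not support:**

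- A reader might infer that every child with a very low single score is misclassified, for example 55 with 86. That follows from how strict the two-composite requirement is. It is a choice of threshold: no less impaired child is classed adverse because of it, and the rewording proposed here leaves it unchanged.
- A reader might infer that accuracy is biased downward. This would follow if the misplaced children had abnormal MR biomarkers, which is plausible but not shown in the document.
- A reader might infer that the sample size is wrong. It reproduces, and the loss of events cannot be quantified.

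**Conclusion.** The point holds as a logical error in the primary outcome as written. A survivor with one composite below 70, the other at 70–84, a listed moderate item, and none of GMFCS 3–5, hearing aids or blindness is classed not adverse. A less impaired survivor with both composites at 70–84 and the same item is classed adverse. No other section of the article repairs this.

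This conclusion rests on the wording alone and needs no distributional assumption. The number of children affected is unknown and may be small. The correction is needed because the reversal lies in the reference standard of the primary analysis, whatever the count proves to be.

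**What to change.** Before outcomes are read, reword moderate disability as: not severe, both cognitive and language composites below 85, and one or more of the listed items. The cut-offs of 70 and 85 stay where they are (assuming whole-number scores, so that at most 84 and below 85 coincide), and a lower score can no longer move a child out of adverse. Report the current wording as a sensitivity analysis, with the number of children whose class changes.

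Separately, the sponsor should confirm whether both or either is intended in the Bayley criterion for severe. That decides how strict the category is and is not needed to remove the reversal.

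The cost is a wording amendment. Every item is already collected at follow-up, so no new data are required.

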### Outcomes

The primary outcome is to examine the accuracy of quantitative cerebral MR biomarkers for predicting adverse 18–24-month neurodevelopmental outcome in infants who had neonatal encephalopathy treated with therapeutic hypothermia, in a multicentre setting.

The secondary outcomes are the intercentre variability of proton MRS measurements and the incremental benefits of quantitative MR biomarkers for predicting adverse outcomes when compared with conventional MR assessment and bedside assessments and investigations such as the Apgar score at 1, 5 and 10 min; umbilical cord pH; base deficit and Lac or blood gas pH; base deficit; Lac within 1 h of birth; abnormal aEEG (voltage criteria: upper margin <10 µV, lower margin <5 µV) at 48 h; neurological examination at discharge.

### Sample size calculation and data analysis

The primary outcome will be unfavourable outcome at 18–24 months (yes/no). Approximately 50% of the infants are expected to have an unfavourable outcome. Since this is binary, multivariable logistic regression will be used to develop risk prediction models. The predictors in these models will be: [NAA], Lac/NAA peak area ratio, white matter FA (all continuous); aEEG at 48h (categorical with three levels) and clinical examination at discharge (binary). Models will be validated using 10-fold cross-validation, and will be assessed with respect to calibration and discrimination. Calibration and discrimination will be measured using calibration slopes and receiver operating characteristic curves, respectively. Shrinkage techniques will be used to adjust for overfitting, thus improving calibration. Sensitivity and specificity will be calculated at selected cut-off points.

The sample size is calculated using the ‘rule of 10’,^2^ generally used to calculate the sample size requirements for developing prognostic models. The multivariable risk model will contain seven predictors that are modelled using nine parameters to examine the incremental benefits of various clinical, bedside (aEEG) and MR biomarkers (conventional MR reporting, MRS peak area metabolite ratios and [NAA]). Considering nine parameters, we require 9×10 adverse events, which suggest that a total sample size of 180 is required.

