While conventional and diffusion-weighted neonatal MRI is currently the main modality used for the assessment of injury and prediction of outcome after neonatal encephalopathy, it is considered subjective and requires considerable time and experience for interpretation. Measurements of basal ganglia or thalamic metabolites by proton MR spectroscopy (MRS), in particular the ratio of lactate/*N*-acetylaspartate (Lac/NAA), have been shown in meta-analyses to be the most accurate cerebral MR biomarkers for predicting medium-term adverse neurological outcome currently available.^16^ Unfortunately, these data come from a very few, small single-centre studies, using a variety of MR sequences on 1.5 T MR scanners,^17–19^ and their applicability over a wider range of centres is not known. There is very little information available on the use of these MRS biomarkers on babies who have received rescue hypothermic neuroprotective therapy and in general have lesser degrees of injury than in earlier cohorts; additionally, there is a lack of data at 3 T, which is expected to be the standard platform for neonatal neuroimaging in the next decade.

Metabolite peak area ratios are affected by pathophysiological changes in both NAA and Lac, which follow very different time courses and which can be variably and independently affected by neuroprotective therapies and intercentre scanner differences.^20^ Hence, despite the good reported prediction of outcome with metabolite ratios, absolute quantification of [NAA], even though technically more challenging to estimate than metabolite peak area ratios, may offer several advantages. NAA is the second most abundant amino acid in the nervous system, and is almost exclusively neuronal. Therefore, it has been used as a surrogate index of neuronal survival. NAA concentrations measured by ^1^H MRS are theoretically absolute, reproducible,^21^ should not vary with scanner magnetic field strength, investigatory centre^20^ and correlate well with NAA concentrations measured by high performance liquid chromatography.^22^
^23^ Therefore, it is considered an ideal biomarker.

Smaller single-centre studies have also shown good correlation of reduced whole brain fractional anisotropy (FA; analysed by Tract Based Spatial Statistics—TBSS) with adverse outcomes at 2 years.^24^

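### The named predictors include no age term and no age-standardised biomarker, although scans are pooled over days 4–14 and 36–43 weeks gestation; measured accuracy of the spectroscopy markers can suffer.

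*Protocol article*

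**What the plan says.** All references are to the Protocol article.

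- **Sample size calculation and data analysis** lists the predictors of the logistic model: "NAA], Lac/NAA peak area ratio, white matter FA (all continuous", then "aEEG at 48h (categorical with three levels) and clinical examination at discharge (binary". Neither age appears, and no age-standardised biomarker value or age-specific cut-off is described. The same section counts seven predictors and nine parameters, so the list is two predictors short.
- **Acquisition**: "MRI will be performed between 4 and 14 days after birth". The exclusion criteria add only "inability to scan within 2 weeks of birth"; no narrower window is set for the quantitative markers.
- **Inclusion criteria**: "Term and near term infants (36–43 weeks gestation".
- **Background**: metabolite ratios are affected by "pathophysiological changes in both NAA and Lac, which follow very different time courses".
- **Conventional MRI score**: the reader is "blinded to the clinical history but not gestational age and age at scan".
- **TBSS analysis** relates FA to outcome and states no age covariate.
- **Clinical assessment** records gestational age for every infant.

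**The concern.** The primary aim is the accuracy of quantitative MR biomarkers. If a marker depends on when the infant is scanned as well as on injury, pooling scans over a wide age range adds variation unrelated to outcome, and discrimination falls. If infants who do badly also tend to be scanned earlier or later, the age effect becomes bias, in either direction.

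The article gives its own reasons to take this seriously. A ratio of two metabolites that change on different clocks can depend on the day it is measured. For conventional MRI, the authors treat both ages as information the reader needs. A secondary outcome is the incremental benefit of the quantitative markers over conventional MR assessment. On the text as it stands, that comparison sets an age-informed reading against markers with no stated allowance for age. The phantom and adult-volunteer phases address differences between scanners and centres and cannot reveal an infant-age effect.

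**Working it through.** **1. The article's sample size.** Nine parameters × 10 events = 90 events; 90 / 0.50 = 180. This reproduces the stated figure exactly.

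**2. What the named predictors use.** Three continuous markers (3) + three-level aEEG (2) + binary examination (1) = 6 parameters from 5 predictors. That leaves 9 − 6 = 3 parameters and 7 − 5 = 2 predictors unnamed. The section's own wording points to conventional MR reporting as one; the other is not identified.

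**3. Age span allowed.** Earliest: 36 weeks + 4 days = 256 days, or 36.6 weeks. Latest: 43 weeks + 14 days = 315 days, or 45.0 weeks. The span is 59 / 7 = 8.4 weeks of postmenstrual age. These are eligibility limits, not an expected distribution.

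**4. Possible loss of accuracy.** For one normally distributed marker with standardised separation d between outcome groups after age adjustment, AUC = Φ(d/√2). If age explains a share R² of within-group variance and is unrelated to outcome, the unadjusted AUC is Φ(d·√(1 − R²)/√2). The article gives neither d nor R², so both are assumed.

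| Age-adjusted AUC | R² 5% | 10% | 20% | 30% | 40% |
|---|---|---|---|---|---|
| 0.75 | 0.745 | 0.739 | 0.727 | 0.714 | 0.699 |
| 0.85 | 0.844 | 0.837 | 0.823 | 0.807 | 0.789 |
| 0.856 (d = 1.5) | 0.849 | 0.843 | 0.829 | 0.813 | 0.794 |
| 0.95 | 0.946 | 0.941 | 0.929 | 0.916 | 0.899 |

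The smallest loss is 0.004 (0.95 to 0.946) and the largest about 0.06 (0.856 to 0.794).

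**5. Possible bias.** Assume scan days uniform over days 4 to 14, so SD = 10/√12 = 2.89 days, and a difference of 1 to 3 days in mean scan day between outcome groups. The shift in the marker is (difference / 2.89) × √R². With R² of 10 to 30%:

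- A marker with no true effect: 1 day and 10% gives a shift of 0.110 and AUC Φ(0.110/√2) = 0.53; 3 days and 30% gives 0.569 and AUC 0.66.
- A marker with a true AUC of 0.85 appears as anything from 0.68 to 0.90, depending on size and direction.

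These are illustrations; no figure on scan timing by outcome is given.

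**6. Cost of entering age in the outcome model.** One extra parameter: 10 × 10 = 100 events, N = 200. Two: 11 × 10 = 110 events, N = 220. With N held at 180, events per parameter become 90/10 = 9.0 or 90/11 = 8.2, below the article's own rule.

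**The case against.** Several counter-arguments have force.

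- **The predictor list is incomplete.** One of the two unnamed predictors is unidentified, so a reader might infer too much in saying that the final model certainly has no age term. That is certain only for the five named predictors. Nothing suggests that the missing one is age.
- **The article condenses a fuller protocol.** Covariates in a TBSS design are often left to that document, and the text says the markers are continuous, not that they enter untransformed. This weakens the TBSS part. It does not remove the main point, because the article chooses to list its model predictors.
- **The Background sentence is about metabolites.** It argues for adding absolute [NAA]; it does not say how far either metabolite moves between days 4 and 14, or with gestation. A reader might infer that all three biomarkers are known to change with age. The document states time dependence for NAA and Lac only; for FA the concern rests on analogy with the age-informed conventional reading.
- **The size is assumed.** A reader might infer that accuracy is shown to be diluted or confounded. It is not: no age effect is quantified and no link between scan timing and outcome is given. With 90 events and 90 non-events, the Hanley–McNeil standard error at AUC 0.85 is about 0.029 (95% half-width about 0.057), so most of the range lies within sampling error. A systematic loss does not average out, however, and would carry into later use of the marker.
- **Unadjusted accuracy is a legitimate target.** It is what a marker achieves when used anywhere in the window. That is a reason to report it alongside, not to omit the adjusted figure.
- **Adding scan age as a covariate could mislead.** If timing is related to outcome, scan age would itself predict outcome and could raise the AUC. This stands, and it decides the form of the fix.

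**Conclusion.** The point holds in a limited form. The named predictors make no allowance for age at scan or gestational age, while the same article pools a 10-day scan window and a 7-week gestation range, describes differing time courses for NAA and Lac, and gives both ages to the conventional reader. The consequence is a possible loss of measured accuracy for the spectroscopy markers of about 0.004 to 0.06 in AUC, and an uneven comparison with conventional MRI. The figures assume a single binormal marker and an age share of 5 to 40% of within-group variance; neither comes from the article, and the planned model is multivariable. Bias from scan timing is possible but not shown. The change is worth making because it is cheap and better fixed before outcomes are known.

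**What to change.** - Standardise [NAA], Lac/NAA and FA on postnatal age at scan and gestational age at birth, with the age relation estimated in the training folds only and then applied to the held-out fold. This adds no parameters to the outcome model, so N = 180 under the rule of 10 is unaffected.
- Do not enter scan age as a free predictor of outcome.
- Add both ages as nuisance covariates in the TBSS comparison of FA by outcome.
- Report unadjusted accuracy alongside, and accuracy by scan window (for example days 4–7 and 8–14), as checks.
- Name the two predictors missing from the list. If one is already age, say so.

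**Cost.** Gestational age is recorded and age at scan is already given to the MRI reader, so no new data are needed. The price is a little more analysis work and some estimation noise in the age slopes, which would come from encephalopathic infants because the volunteer phase scans adults.
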